#### Procedures for patient recruitment and data collection

Managers of inpatient services selected for potential participation will be contacted by the research team via telephone and/or email to explain the purpose of the study, why their service has been selected, and what would be required of the manager, the staff, and the patients if they agree to participate in the study.

Once a service has agreed to participate, the research team and service manager will arrange a time for the researcher to visit the inpatient service to recruit participants and collect data. It is expected that the researchers will spend approximately one week in each service. The researcher will interview the service manager to collect service level data. The researcher will also meet with the rehabilitation unit staff to explain the purpose and processes of the study. Staff will be asked to approach eligible patients and asked if they would like to meet the researcher to discuss the study.

Informed consent will be collected from patients who have capacity and agree to participate. The patient research interview will then be conducted and once completed, the patient will be offered £20 for their participation [30].

All efforts will be made to maximise the capacity of each patient to be able to provide informed consent for the study (for example, by explaining the purpose and process of the study in simple terms and over multiple meetings), and any patient with capacity who declines participation will not be included. However, for eligible patients who lack capacity to give informed consent we will seek advice from a consultee on their participation. Research data for participants lacking capacity will be collected via staff interview and healthcare records, but these participants will not be asked to participate in an interview themselves.

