#### Procedure and data collection

We will follow participants recruited in C1 for 18 months and compare total inpatient days from recruitment, including any readmissions, for those in NHS and independent sector units. To account for the fact that independent sector patients are likely to have less time to relapse (due to longer admissions) than those in NHS units, our main analysis will compare readmissions for those discharged during the 12-month recruitment period in C1. However, we will also conduct a supportive analysis including all patients discharged during the 18-month follow-up period.

We have successfully tracked similar patient cohorts and will gain participants’ consent for this at recruitment in C1. We plan to follow their progress through contact with key staff and will record contact details for these staff at recruitment into C1 (including the participant’s local CCG and NHS Trust and their community care co-ordinator or care manager). We will contact the manager of inpatient rehabilitation units that participated in C1 every month to confirm whether any patient participants have been discharged or transferred to another inpatient unit. Where this is the case, we will record the date of transfer/discharge and details of where the patient has moved to and confirm contact details for key staff involved in their ongoing care such as their community care co-ordinator. This staff member will be the patient participant’s ‘key staff contact’ for the remainder of the study and we will continue to keep in contact with them monthly to track the patient’s progress and the dates of any further admissions. We will collect from the key staff contact at six, 12 and 18 months details following discharge about the patient’s use of mental health supported accommodation (residential care, 24 h supported housing, < 24 h supported housing), the number of hours and cost per week of any additional ‘care packages’ funded by the NHS or social services that are in place to support them in the community and the length of time any such care packages have been in place, any readmissions (including general medical admissions), number of visits to Accident and Emergency, and the number of community contacts.

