#### Sample size estimation

We aim to recruit 500 participants. A sample of 294 (half from NHS and half from independent sector units) will allow us to detect a mean difference in inpatient days of 0.38 SD (REAL study SD = 113, i.e. around 6 weeks) [7] between NHS and independent sector rehabilitation units, using a two-sample t test with 90% power and 5% significance level. Based on a bed day cost of £350, 6 weeks is an important difference, representing a potential saving of £14,700 per patient.

To perform the multivariable regression analysis described below, this sample size is increased to 350 after inflating, using a variance inflation factor (VIF) of 1.19 (derived using a multiple correlation coefficient of 0.16, the assumed proportion of variance in the service type explained by its association with the confounding variables). We do not have estimates available for the VIF from previous studies and thus assumed a moderate strength of association between service sector and the confounding variables [34]. The sample size further increases to 497 after allowing for a design effect (DE) of 1.42 (based on an average cluster size of 8 and an intracluster correlation of 0.06) [4].

Based on the REAL cohort study findings [7] and CQC report [9, 35], we estimate 160 NHS and 80 independent sector patient participants will be discharged during the 12 month recruitment period in C1 (without readmission) and around 33% NHS patients will be readmitted during follow-up. Thus, for our main secondary outcome, this sample size (240 patients) will allow us to detect a difference in readmission of 22.3% between NHS and independent sector units with 90% power or 19.7% with 80% power (based on a Z-test comparing two proportions) and 5% significance level assuming the same VIF and DE as above.

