#### Analysis

We will conduct two statistical analyses using the information collected from C1 and C3:

i.Multivariable regression

We will conduct linear regression using total inpatient days (since recruitment to C1) as our primary outcome and logistic regression using proportion of patients readmitted as our main secondary outcome, allowing for clustering within inpatient rehabilitation units. Service sector (independent or NHS) will be included in the model as the main explanatory variable. We shall adjust for relevant sociodemographic and clinical confounding variables, including inpatient days up to recruitment (gathered in C1), which may account for differences in outcomes between the two service types. We will use Directed Acyclic Graphs (DAGs) to ensure a logical and consistent approach to identifying potential confounders [36]. Suitable transformations will be used if assumptions of normality for linear regression are not satisfied. In addition, we will conduct exploratory analysis to investigate the relationship between the length of the inpatient rehabilitation admission (i.e. ‘dose’ of rehabilitation assessed in inpatient days), readmission and the service sector (independent or NHS), through a mediation analysis. Bias due to missing data in the explanatory variables (gathered in C1) will be investigated and we will use multiple imputation based on chained equations to impute missing values for these variables as appropriate.

ii.Multivariable regression with propensity score

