### Component 5: Health economic evaluation calculating the relative cost effectiveness of inpatient rehabilitation services provided by the NHS and the independent sector 

Component 5 (C5) will address research question 5:

5.Is inpatient rehabilitation more cost effective when provided by the independent sector or the NHS, after adjusting for differences between the sectors in terms of key predictors of costs such as patient characteristics and length of stay?

The main cost-utility analysis (CUA) will use information from C1 and C3 to calculate the incremental cost per quality-adjusted life-year (QALY) gained by using independent sector rehabilitation services compared to NHS rehabilitation services, over the 18-month period. The largest costs are expected to be due to inpatient rehabilitation days (i.e. the primary statistical outcome), but the cost perspective will also include other NHS and Personal Social Services resource use to describe the wider support provided to participants.

The supporting cost-effectiveness analysis will calculate the incremental cost per readmission avoided (this is the secondary statistical outcome) for those discharged during the 12-month recruitment period in C1/C3. We will also conduct a supportive analysis including all patients discharged during the 18-month follow-up period of C1/C3.

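### The main readmission analysis in Component 3 leaves time at risk unequal (6 to 18 months), selects on discharge, and rests on an undefined 12-month window and a power statement that holds only for a lower independent-sector rate

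*Protocol article*

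**What the plan says.** Component 3, Procedure and data collection, gives the reason for restricting the analysis: "independent sector patients are likely to have less time to relapse (due to longer admissions"). It then says "our main analysis will compare readmissions for those discharged during the 12-month recruitment period in C1", and adds that "we will also conduct a supportive analysis including all patients discharged during the 18-month follow-up period". Follow-up is per person: "We will follow participants recruited in C1 for 18 months".

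Component 3, Analysis (i), names the model: "logistic regression using proportion of patients readmitted as our main secondary outcome". It allows for clustering by unit and adjusts for confounders, including inpatient days up to recruitment. It gives no fixed post-discharge window and no term for time at risk.

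Component 3, Sample size estimation, says "we estimate 160 NHS and 80 independent sector patient participants will be discharged during the 12 month recruitment period in C1 (without readmission"). It takes 33% readmission for NHS patients. From these 240 patients it derives detectable differences of 22.3 points (90% power) and 19.7 points (80% power), using a Z-test for two proportions with VIF 1.19 and design effect 1.42.

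Component 5 reuses the same set for its supporting analysis, the "incremental cost per readmission avoided (this is the secondary statistical outcome) for those discharged during the 12-month recruitment period in C1/C3".

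**The concern.** There are four linked problems.

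1. **Window.** The 12-month recruitment period reads as calendar time. Component 1 says "It is expected that the researchers will spend approximately one week in each service", and 500 patients at about 8 per unit means some 62 units, so recruitment is presumably staggered. A patient recruited in month 1 would then have about 11 months in which to be discharged into the set; one recruited in month 11 would have about one.
2. **Exposure.** Restricting the discharge date limits the spread of time at risk but does not equalise it, and logistic regression treats all retained patients alike.
3. **Selection.** Discharge is itself affected by sector. If the independent sector discharges half as many patients, those discharged may be a more selected, less severe group. Covariate adjustment removes only the measured part of that.
4. **Power.** The parenthesis about no readmission sits beside a 33% readmission rate, and the basis of 160 and 80 is not given.

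This outcome is the direct answer to research question 4, which asks which sector better prevents readmission. A sector that discharges fewer patients, and later, could appear to have fewer readmissions without better care.

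**Working it through.** **Inputs from the article.** 250 patients per sector; 160 and 80 discharged, so 160/250 = 64% and 80/250 = 32%; NHS readmission 33%; VIF 1.19; design effect 1.42; two-sided 5% (two-sided is assumed); 18 months of follow-up from recruitment.

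**Step 1: the stated detectable difference.** The combined inflation is 1.19 × 1.42 = 1.690. For effective sizes n1 and n2, power = Φ[(d − 1.96·SE0)/SE1], where SE1 = √(p1q1/n1 + p2q2/n2) and SE0 uses the pooled proportion.

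- *Equal split, 120:120.* Effective n is 71.0 per group. The difference needed is 22.2 points at 90% and 19.7 at 80%. At 22.3 points (33% v 10.7%), SE0 = 0.0693 and SE1 = 0.0668, giving power 90.4%; at 19.7 points, 80.1%. The stated figures reproduce.
- *Stated split, 160:80.* Effective n is 94.7 and 47.3. At 22.3 points, SE0 = 0.0776 and SE1 = 0.0660.

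| 160:80, independent rate | Needed at 90% | Needed at 80% | Power at 22.3 | Power at 19.7 |
|---|---|---|---|---|
| lower, pooled | 23.4 | 21.0 | 86% | 73% |
| lower, unpooled | 21.6 | 19.4 | 92% | 81% |
| higher, pooled | 28.2 | 24.5 | 72% | 62% |
| higher, unpooled | 27.8 | 24.3 | 73% | 62% |

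**Step 2: range of time at risk.** Time at risk = 18 − (months from recruitment to discharge). Under either reading of the window, a retained patient is discharged 0 to 12 months after recruitment, so time at risk runs from 18 down to 6 months.

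**Step 3: spurious difference from time at risk alone.** Assumptions not in the article: exponential discharge reaching 64% and 32% at 12 months from each patient's recruitment, uniform recruitment, and the same constant readmission hazard in both sectors, set so that the NHS proportion in the main set is 33%.

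- Calendar window: mean time at risk 14.6 v 14.3 months; readmitted 33.0% v 32.3%, a gap of 0.7 points (0.5 to 1.6 over other discharge shapes).
- Per-participant window: 13.0 v 12.4 months; 33.0% v 31.7%, a gap of 1.3 points.
- 18-month supportive analysis: about 3 to 4 points, depending on which set is calibrated to 33%.

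**Step 4: adding selection.** Let a normally distributed severity, not adjusted for, slow discharge and speed readmission with the same log-hazard slope. With no true sector effect, the apparent independent-sector advantage is:

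| Assumed slope | Calendar | Per participant |
|---|---|---|
| 0 | 0.7 | 1.3 |
| 0.5 | 1.9 | 3.0 |
| 1.0 | 5.5 | 7.0 |

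A time-to-readmission analysis removes the first row but not the others. In the per-participant set the readmission rate ratio, with no true effect, is still about 0.95 at slope 0.5 and about 0.8 at slope 1.0.

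**Step 5: yield, if 64% and 32% are per-participant 12-month figures (an assumption).** With x = −ln(1 − p), the share discharged inside a calendar window is 1 − (1 − e^(−x))/x, which is 37.4% and 17.0%. That gives 93 + 43 = 136 patients. Weibull shapes 2 to 0.5 give 93 to 176. With 136, power for a 22.3-point fall is 58% (pooled) or 72% (unpooled). Conversely, for a calendar window to yield 160 and 80 under exponential discharge, about 92% and 56% would have to be discharged within 12 months of recruitment.

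**The case against.** A reader might infer that the plan cannot deliver its 240 patients. The article does not support that. It gives 160 and 80 for this very period, citing earlier data that are not shown, and does not say whether they are calendar or per-participant figures. If the window is per participant, 240 may stand. The shortfall in step 5 is conditional.

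A reader might also infer a large bias. Time at risk alone contributes about one point against a 22.3-point target, and the restriction does reduce the problem compared with the supportive analysis. The larger figures come from assumed slopes and ignore the planned covariate and propensity adjustment, which draws on extensive baseline severity data.

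Nor is the stated power figure shown to be wrong for a lower independent-sector rate. The article does not name the variance form, and 22.3 lies between the unpooled and pooled answers for 160:80.

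Other parts of the plan limit the damage. Total inpatient days, the primary outcome in Component 3, covers everyone. Discharge without readmission is already part of successful rehabilitation, the outcome of the propensity score analysis. A mediation analysis of length of stay is planned. The main economic analysis is cost per QALY; cost per readmission avoided is only supporting. The parenthesis may mean no readmission within the recruitment period.

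These points reduce the size of the concern. They do not define the window, equalise exposure in the named model, or cover a higher independent-sector rate.

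**Conclusion.** The concern holds in a limited form. Three parts need no outside assumption: the window is not defined, time at risk spans 6 to 18 months under a model that ignores it, and the set conditions on discharge, which the article expects to differ two to one between sectors. The power statement holds at best for a lower independent-sector rate. For a higher rate, which research question 4 leaves open, 160:80 needs about 28 and 24.5 points, and power at 22.3 points is 72% to 73%.

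The bias from unequal time is small (0.7 or 1.3 points). Selection on discharge is potentially larger, about 2 to 7 points, but that range rests entirely on assumed severity slopes. The reduced yield of 93 to 176 patients applies only if 160 and 80 are per-participant figures and the window is calendar time.

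**What to change.** - Define the set as patients discharged within 12 months of their own recruitment, which guarantees at least 6 months of scheduled follow-up after discharge. State that 160 and 80 are on that basis, or re-estimate them.
- Replace logistic regression with time from discharge to first readmission, censored at end of follow-up, allowing for clustering by unit. Make the two changes together: the per-participant window with plain logistic regression would roughly double the time-at-risk bias (0.7 to 1.3 points).
- Because this does not remove selection on discharge, report alongside it the proportion discharged without readmission by 18 months among all 500. Interpret the discharged-only result and the supporting cost per readmission avoided in that light.
- Clarify the without-readmission parenthesis against the 33% rate.
- Restate the detectable difference for 160:80, naming the variance form, in both directions.

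The cost is small: discharge and admission dates are already tracked monthly, so the change is wording plus one added model. The downside is a less favourable stated detectable difference.

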Quality-adjusted life-years (QALYs) will be calculated from patients’ utility scores captured in C1 and C3 over the 18-month period, calculated in turn from EQ-5D-5 L (a 5-item generic health-related quality-of-life questionnaire plus visual analogue scale) responses using standard methods and a secondary analysis will calculate these from ReQOL (the 10-item Recovering Quality of Life questionnaire designed for users of mental health services) responses. These two quality-of-life questionnaires will be completed with patient participants at recruitment (C1) and through telephone or videoconferencing at 6, 12 and 18 months follow-up (C3). We will use the resource use data gathered via the key staff contact about patient participants discharged from the inpatient rehabilitation unit they were receiving treatment in at recruitment, as well as the inpatient costs pre-discharge, to calculate costs and quality-adjusted life-years per patient. These resources include the length of the baseline inpatient rehabilitation admission from the study baseline date (i.e. the date the patient participant was interviewed for C1), any readmissions in days, the use of supported accommodation services (including the length of time the participant has lived there, the level of support provided [residential care, 24 h supported housing, < 24 h supported housing] and the weekly costs) and any individual ‘care packages’ provided, including the number of hours of support per week, the cost per week and the length of time provided. Unit costs for inpatient bed-days will be calculated using a bottom-up microcosting in the first instance so that the independent and NHS services are assessed according to the cost to the provider of providing the services.

C5 will also include cost efficiency analyses using information on inpatient rehabilitation bed-days from C1, C3, and C4, calculating the mean and marginal costs per patient across the two types of service provision, to further investigate the impact of service type around the primary statistical outcome of total inpatient days.

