#### Analysis

The primary analysis perspective will be that of the NHS plus Personal Social Services, so rehabilitation costs for users of NHS services will be captured as number of inpatient days, monetised using unit costs that we will calculate from a bed-day micro-costing across the two arms. Secondary analyses will use (i) published NHS unit costs also for the inpatient rehabilitation costs in both arms, and (ii) the cost charged to the relevant CCG for users of independent sector rehabilitation services. Other health and social care resource use provided after discharge will be costed according to NHS Reference Costs and Personal Social Service Research Unit (PSSRU) unit costs [40] for all analyses. QALYs will be calculated from utility scores using standard area-under-the-curve methods and adjusted for baseline values.

The bed-day micro-costing will use certain items from the QuIRC (avoiding duplication of questions), supplemented by other information from the key staff contact or team in order to provide a mean unit cost per patient for the two settings, including: staffing levels and salaries (mean cost per hour, also consider holiday pay, sick leave, etc.); staff to patient ratios; number of patients per ward; number of patients on ward with similar diagnosis; estates costs and other overheads (including ward floor square metres); medication costs; ‘hotel’ facilities (food, laundry etc.); travel or other similar costs (e.g. to visit local area, to access community resources). The questions will be developed with the independent providers and staff at NHS sites to ensure they are appropriate and will yield meaningful information.

Bootstrapping will be used to calculate means and 95% confidence intervals for costs and QALYs to show the probability that rehabilitation in the independent sector is cost-effective compared to in the NHS for a range of cost-effectiveness threshold values. We will report a cost-effectiveness plane (CEP) and cost-effectiveness acceptability curve (CEAC) using the bootstrapped results.

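### A&E visits, general medical admissions and outside contacts are collected and costed only after discharge, so the longer-stay sector is observed for less time on these items

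*Protocol article*

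**What the plan says.** The Component 3 section on procedure and data collection sets the follow-up of resource use: "We will collect from the key staff contact at six, 12 and 18 months details following discharge about" supported accommodation, care packages and "any readmissions (including general medical admissions), number of visits to Accident and Emergency, and the number of community contacts". The informant is a key staff contact, a role that the same section assigns once a participant has been discharged or transferred.

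Component 5 takes this up in the same form: "We will use the resource use data gathered via the key staff contact about patient participants discharged from the inpatient rehabilitation unit" where they were at recruitment, "as well as the inpatient costs pre-discharge". Its Analysis section adds: "Other health and social care resource use provided after discharge will be costed according to NHS Reference Costs" and the standard published social care unit costs.

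The opening of Component 5 describes an 18-month cost-utility analysis and says that "the cost perspective will also include other NHS and Personal Social Services resource use".

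The Component 3 sample size section supplies the expected difference in discharge: "we estimate 160 NHS and 80 independent sector patient participants will be discharged during the 12 month recruitment period in C1", specified there as discharges without readmission.

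**The concern.** Whether an emergency visit or a general hospital admission is recorded depends on whether the participant has already left the baseline unit. Discharge timing is closely tied to sector: the Background reports independent-sector admissions about twice as long as NHS ones, and the plan expects half as many independent-sector discharges. Time at risk for these items is thus shorter in one group by design. If they are summarised or costed per patient over 18 months, equal underlying rates will give lower figures in the independent sector.

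The plan sees the same mechanism elsewhere. For readmission, it notes that independent-sector patients will have less time to relapse and restricts the main analysis to those discharged in the first 12 months. No matching step is described for the outside-care items. Here the time is not truly missing, because every participant is followed for 18 months and could be asked about all of it.

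At stake are the non-bed part of the cost-utility analysis and any comparison of these counts between sectors. Events that were never recorded cannot be recovered in the analysis.

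**Working it through.** **Is the gap filled elsewhere?**

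- Component 1, measures: contacts with external professionals are asked once, at baseline, for the previous three months, in the patient interview.
- Component 3, follow-up interviews: only ReQOL and EQ-5D-5L are repeated.
- Component 3, monthly calls to unit managers: these establish discharge or transfer. A general hospital stay might surface this way, but not as a costed item.
- Component 5, bed-day micro-costing: the listed items are staffing, estates, medication, hotel facilities and travel. A&E and general hospital care are not among them.

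The collection wording can mean fixed dates after recruitment, or dates counted from discharge. Either reading excludes time before discharge.

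**How unequal is observed time?** The plan gives no figure, so it is derived.

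Inputs: 250 participants per sector (Component 1, sample size); 160 NHS and 80 independent-sector discharges in 12 months (Component 3, sample size estimation); 18 months of follow-up. Assumptions: a constant discharge rate, the 12-month counts treated as discharges within 12 months of entry, and time after readmission ignored.

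With p the proportion discharged by 12 months, the monthly rate is h = −ln(1 − p)/12. Mean time before discharge over 18 months is m = (1 − exp(−18h))/h.

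- NHS: p = 160/250 = 0.64, h = 0.0851, m = 9.21 months (51%); observed 18 − 9.21 = 8.79 months (49%).
- Independent: p = 80/250 = 0.32, h = 0.0321, m = 13.67 months (76%); observed 4.33 months (24%).
- Ratio of observed time, NHS to independent: 8.79/4.33 = 2.03.

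**Sensitivity to the assumptions**

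| Assumption | Observed, NHS (months) | Observed, independent (months) | Ratio |
|---|---|---|---|
| Constant discharge rate, 160 and 80 of 250 | 8.79 | 4.33 | 2.03 |
| Constant number of discharges per month | 8.64 | 4.32 | 2.00 |
| 25% more discharges, constant rate | 11.21 | 5.43 | 2.06 |
| 25% more discharges, constant number | 10.50 | 5.40 | 1.94 |
| Staggered entry, about 6 months' average exposure | 12.40 | 7.33 | 1.69 |
| Mean stay 2:1, NHS mean 6 months | 12.30 | 8.68 | 1.42 |
| Mean stay 2:1, NHS mean 24 months | 5.34 | 2.99 | 1.79 |

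For staggered entry the divisor 12 in h becomes 6. This gives m = 5.60 months (31%) for the NHS and 10.67 (59%) for the independent sector. The ratio is roughly 1.4 to 2 throughout, and its direction never changes.

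**How much could this move total cost?** The plan's benchmark reproduces: 42 days × £350 = £14,700. In the first scenario the difference in unobserved time is 13.67 − 9.21 = 4.46 months per patient. Unrecorded outside care would have to cost £14,700/4.46, about £3,300 per month, to create a bias of that size. The bed-days in the same 4.46 months are fully counted and come to 4.46 × 30.44 × £350, about £47,500.

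**The case against.** The strongest reply is that little of consequence depends on these items. Bed-days are counted from recruitment in both sectors and are expected to be the largest cost. ReQOL and EQ-5D-5L are sought from everyone at 6, 12 and 18 months. Supported accommodation and care packages properly arise after discharge, so much of any higher non-bed cost in the NHS group would be real. All of this stands.

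A reader might infer that the longer-stay sector will look safer and cheaper. The documents do not support that. No safety outcome or safety analysis is described; these events appear as resource use. On total cost, the dominant component is fully counted and runs against the longer-stay sector, so the omission only trims its incremental cost. Nor is most of the follow-up unobserved in general: that holds only for outside-care items, and about half of NHS time is unobserved for them too.

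A firm twofold ratio is also more than the figures bear. The 160 and 80 are planning estimates of discharges without readmission during a recruitment period, not all discharges within 12 months of each entry. Equal event rates inside a staffed unit and in the community are an assumption as well.

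Finally, this is a condensed article and the forms are not shown, so they may ask more. But the restriction is not a silence: three separate statements on collection, population and costing all confine these items to the period after discharge. The general statement of perspective is broader than those details, so the text falls short of its own aim.

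**Conclusion.** The point holds for a limited set of items: A&E visits, general medical admissions and external or community contacts during the baseline admission. As written, they are neither collected nor costed, and the time lost is greater in the independent sector. Observed shares are about 24% against 49% of 18 months under a constant discharge rate from the plan's own estimates, with a ratio of roughly 1.4 to 2 across the assumptions tried. At equal true rates, per-patient counts and non-bed costs would be understated more in the independent sector, and its incremental cost slightly understated. Bed-days and quality of life are not affected, and the effect on total cost is likely small. The stated 18-month perspective and the costing rule need to be reconciled. This is a cheap improvement, not a threat to the main comparison.

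**What to change.** In the Component 3 data collection section and in the resource-use and Analysis text of Component 5, specify that A&E visits, general hospital admissions and external professional contacts are collected at 6, 12 and 18 months from recruitment for every participant. The unit or ward manager would supply them while the participant is an inpatient, and the care co-ordinator after discharge. Cost them over the full 18 months. Keep supported accommodation and care packages as post-discharge items. Observed time then becomes 18 months in both sectors, with no change to the sample size.

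The route exists: unit managers are already contacted monthly, and the follow-up text names the ward manager as the contact for inpatients. The cost is a few more questions and slightly longer contacts.

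The article does not say how far follow-up has progressed. If in-unit data can no longer be collected, report these items per post-discharge person-time and add a sensitivity analysis for outside care during admission, for example using the baseline three-month external contacts. Restate the cost perspective at the start of Component 5 to match what is measured.
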